**Figure 3. f3:**
[figure not shown]
Schedule of events.

### Data management

Data will be recorded in a pseudo-anonymised form in a password protected database. Documents containing personal information and signed consent forms will be kept in a locked file at the principal investigator’s office at each centre. Data will be added to the electronic database by authorised team members only and access will be limited to authorised team members. No participant will be identified or will be identifiable as a result of data processing or in any subsequent publication. Data will be destroyed 5 years after the end of the study or 3 years after the last publication as per the guidelines described by the research ethics committee of the Irish College of General Practitioners. The lead PI (JT) will be the data controller. Data processors will be the research team members, including the 6 co-investigators in each of the centres.

### Method of assigning participants to treatment groups

***Randomisation*.** Randomisation of participants will be done on a 1:1 allocation to intervention or usual care by a simple randomisation procedure, guided by the Clinical Research Centre (CRC) team. We will use a randomisation software product provided by the American National Cancer Institute.

### Definition of end-of-trial

The end of trial will be the date of the last visit of the last subject. The trial team has the right at any time to terminate the study for clinical or administrative reasons. The end of the study will be reported to the REC within 90 days. A summary report of the study will be provided to the REC and Regulatory Authority within 1 year of the end of the study.

***Premature termination of the study*.** The trial team may end the study pre-maturely on the basis of new information about safety of the intervention or unsatisfactory progress in enrolling participants (i.e., <50% of sample size after 6 months).

### Discontinuation/withdrawal of subjects from study protocol

Subjects have the right to voluntarily discontinue the intervention or withdraw from the study at any time for any reason without any consequences. The investigator has the right to discontinue a subject from study treatment or withdraw a subject from the study at any time if it is in the best interest of the subject.

Subjects must discontinue the intervention and be withdrawn from the study for any of the following reasons:

-   withdrawal of consent by the subject

-   any medical condition that the investigator or sponsor determines may jeopardize the subject’s safety if she or he continues receiving the study treatment

-   ineligibility (either arising during the study or retrospectively having been overlooked at screening)

-   an adverse event which requires discontinuation of the intervention

-   lack of compliance with the study and/or study procedures

-   lost to follow-up. At least three documented attempts must be made to contact any subject lost to follow-up.

If a subject is withdrawn before completing the study, the reason for withdrawal must be documented. If a subject is withdrawn due to an adverse event, the investigator will arrange for follow-up visits until the adverse event has resolved or stabilised.

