### Feasibility study

Feasibility of the exercise component of the intervention was assessed in a study in 2019 and 2020
^12^. The findings have been key to refining the intervention for this RCT. We offered an exercise intervention to reverse frailty and build resilience in primary care consultations. We set out to assess uptake of the exercise regime; ratings of its ease and subjective health after participation; how a follow-up telephone-call might affect compliance and overall feasibility. We applied the Bowen feasibility model
^13^ which has been successfully used in assessing public health and preventive medicine interventions. This feasibility model tests eight areas of focus: acceptability; demand; implementation; practicality; adaptation; integration; expansion; and limited-efficacy testing. Selected results include:

A total of 94 of 107 eligible people (88%) participated (average age 77, 59 females (63%)). 95% of females and 78% of males enrolled. Only 15% had previously considered resistance exercises.

Participants found the exercises both easy to follow and generally easy to do. Overall, 32% described exercises as ‘very easy’, 55% ‘somewhat easy’, 7% ‘neither easy nor hard’, 6% ‘somewhat hard and 0% ‘very hard’.

At one month, 66% of participants called were exercising regularly (76% of females, 50% of males). At two months, compliance among those who had not been called at one month was: 65% (67% of females, 62% of males). However, compliance among those previously called was higher: 78% (88% of females, 63% of males). 64% of those who were not doing exercises at one month had taken them up following the single phone call (67% of females, 63% of males).

Many described how the home-based exercises helped with staying active and reducing anxiety while housebound during the Covid-19 pandemic

The majority of participants self-reported their general health had improved as a result of doing the exercises and none reported feeling worse. 14% felt ‘much better’, 52% ‘slightly better’, 34% ‘about the same’, 0% ‘slightly worse’, and 0% ‘much worse’

Each of the eight areas of focus of the Bowen feasibility model have been addressed and satisfy overall feasibility. Publication of this feasibility study is pending.

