***Secondary outcomes***

 Clinical frailty status measured by CFS at three months after the start of intervention. Muscle mass measured by bioelectrical impedance at three months after the start of intervention.Body fat, bone weight, base metabolic rate, biological age by bioelectrical impedance at three months after the start of intervention. Incidence of in-patient hospitalisation during follow-up. Incidence of long-term care admission (LTC) during follow-up. Ease of the intervention measured on a five-point scale: ‘very easy’, ‘somewhat easy’, ‘neither easy nor hard’, ‘somewhat hard’, or ‘very hard’ three months after the start of intervention. Difference to general health as a result of the exercises measured on a five-point scale: ‘much better’, ‘slightly better’, ‘about the same’, ‘slightly worse’ or ‘much worse’ three months after the start of intervention.

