***Exclusion criteria***

 Rockwood clinical frailty scale score > 5 End of life care Persons in residential care home Concurrent malignancyChronic kidney disease, stage 3 or 4 Coded diagnosis of severe dementia as per GP or consultant geriatrician diagnosis or baseline Montreal Cognitive assessment (MoCA) score ≤ 10 Persons unable to engage in discussion on frailty due to acute care needs or determined to be inappropriate by GP (e.g., needing transfer to ED or acutely unwell or disorders resulting in intolerance of the intervention) Subjects unable to provide written informed consent

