### Analysis sets

Final analysis for this trial will be conducted on the intention-to-treat population, which will include all subjects randomised to the treatment arms. Sensitivity analysis will be conducted on the per protocol population (full analysis set), which will include all subjects that attend all study visits and have complied with the intervention.

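### Compulsory withdrawal from the study, not only from the intervention, loses three-month outcomes that the intention-to-treat analysis needs

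*Protocol article*

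**What the plan says.** The section on discontinuation and withdrawal opens by treating stopping the intervention and leaving the study as two different acts. It then joins them in a compulsory rule: "Subjects must discontinue the intervention and be withdrawn from the study for any of the following reasons". Among the grounds listed are:

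- "lack of compliance with the study and/or study procedures"
- "ineligibility (either arising during the study or retrospectively having been overlooked at screening"
- an adverse event that requires the intervention to be stopped.

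Elsewhere the protocol says:

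- **Analysis sets:** "Final analysis for this trial will be conducted on the intention-to-treat population, which will include all subjects randomised to the treatment arms". Compliance with the intervention is a condition only for the per-protocol set, which serves as a sensitivity analysis.
- **Study methods, assessments and procedures:** all participants are invited back at three months for the outcome assessment. Only intervention participants are called, at one and three months, and asked whether they followed the exercises and diet.
- **Exclusion criteria:** these include CFS above 5 and "Persons in residential care home".
- **Secondary outcomes:** these include CFS at three months and "Incidence of long-term care admission (LTC) during follow-up".
- **Reporting procedures for all adverse events:** an end-of-study assessment is required when a participant is removed or withdraws because of an adverse event. No such requirement appears for the other grounds.
- **Missing data:** chained-equations imputation, where appropriate.

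**The concern.** An intention-to-treat analysis needs outcomes on everyone randomised, whether or not they kept to the intervention. The withdrawal rule ends data collection for some of them because of what happened after randomisation. Three of its grounds can be related to arm or to outcome:

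- An adverse event that stops the intervention can arise only where there is an intervention to stop.
- Compliance with the exercises, if that is meant, is asked about in one arm only.
- Ineligibility arising during the study can be the result of getting worse.

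At stake is the three-month SHARE-FI comparison, together with CFS and muscle mass. If the people removed differ from those who stay, and removal differs between arms, the observed data drift towards the per-protocol set while still being reported as intention-to-treat. An analysis plan written later cannot recover measurements that were never taken.

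**Working it through.** **1. The plan's own figure.** Inputs from the sample size section: 15% v 3% becoming non-frail, alpha 0.05 (taken as two-sided), power 80%, ratio 1, dropout 15%.

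n per arm = [1.96·√(2·0.09·0.91) + 0.8416·√(0.15·0.85 + 0.03·0.97)]² / 0.12² = (0.793 + 0.333)² / 0.0144 ≈ 88.1

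This is 89 per arm or 178 in total when rounded up. The plan states 176, and 88 per arm gives power 0.80. For dropout, 176/0.85 = 207.1, or 208 as an even number, against 210 stated. The sample size reproduces, so the point does not rest on a sample-size error.

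**2. The sections side by side.**

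- *Withdrawal rule v Analysis sets.* A per-protocol set defined by compliance differs usefully from the intention-to-treat set only if non-compliers reach the three-month visit. The withdrawal rule removes non-compliers before it.
- *Withdrawal rule v three-month visit.* One section invites everyone back. The other takes some of them out of the study first.
- *Withdrawal rule v Exclusion criteria and Secondary outcomes.* A participant admitted to a care home meets an exclusion criterion, so becomes ineligible during the study and must be withdrawn. That admission is itself an outcome of the trial. The participant's three-month SHARE-FI, CFS and muscle mass are then not collected.
- *Ineligibility overlooked at screening.* This is a fact from before randomisation, so it need not be related to outcome. It still removes randomised people from a set defined as all randomised.
- *Repair.* The end-of-study assessment covers adverse-event cases only, and the text does not place it at three months. Chained-equations imputation as usually run assumes that data are missing at random given what was recorded. Losses that depend on compliance or worsening may not satisfy that.

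**3. A ceiling on the number removed for non-compliance.** Assume that lack of compliance includes not exercising, that the feasibility rates apply, and that every such person is withdrawn. The Feasibility study section reports: "At one month, 66% of participants called were exercising regularly". It gives 78% at two months among those who had been called. Non-adherence is therefore 34% and 22%. With 210/2 = 105 per arm:

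- 105 × 0.22 = 23.1, about 23
- 105 × 0.34 = 35.7, about 36
- dropout allowed: 105 × 0.15 = 15.75, about 16 per arm

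All 23 to 36 would come from the intervention arm.

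**4. Effect on power at that ceiling.** Add the ordinary 15% dropout, analyse only those observed, and keep 15% v 3%. Control: 105 × 0.85 = 89. Intervention: 105 × 0.85 × 0.78 = 70, or 105 × 0.85 × 0.66 = 59. Power is 0.77 with 70 v 89 and 0.74 with 59 v 89, against 0.80 planned.

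**5. Bias.** With observed cases only, the shift in an arm mean is the fraction removed times the outcome gap between those removed and the whole arm, divided by the fraction kept. The protocol does not give the gap. Two illustrations at the ceiling show how far the answer depends on assumption:

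- No true effect, 3% improve in each arm, none of those removed would have improved: 0.03/0.78 = 3.8% to 0.03/0.66 = 4.5% among those kept.
- True rate 15% in the whole intervention arm, 3% in those removed: (0.15 − 0.22 × 0.03)/0.78 = 18.4% to (0.15 − 0.34 × 0.03)/0.66 = 21.2% among those kept.

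Neither is an estimate for this trial.

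**The case against.** Several stronger readings are tempting, and the documents do not support them.

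- **That everyone who does not exercise must be withdrawn, so the trial compares adherers with all controls.** The ground speaks of compliance with the study or its procedures, while the per-protocol definition speaks of compliance with the intervention. The first can be read as failure to attend or take part in assessments, which applies to both arms. Having a per-protocol set at all favours that reading. Timing also limits the harsher one. In the text, adherence is asked about at one and three months, and the three-month call falls when the outcome visit is due, so only the one-month call clearly precedes it. In the feasibility study 64% of those not exercising at one month took it up after the call. Nothing in the description of the calls links a negative answer to withdrawal, and no two-month check, the source of the 78%, is described for this trial. This stands: 23 to 36 is a ceiling under one reading.
- **That CFS progression is cut off by design.** The text describes CFS at baseline and three months only. A CFS of 6 would usually be found at the visit that records the outcome.
- **That long-term care and hospital events are lost.** The reason for withdrawal must be documented, and hospitalisation is a serious adverse event reportable within 24 hours. These events would probably be recorded.
- **That the intention-to-treat set is formally contradicted.** It still counts everyone randomised, and missing values may be imputed. One-month adherence and withdrawal reasons could inform that imputation, and its model may be in the analysis plan.

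These arguments reduce the size of the problem. They leave the rule itself in place: it is compulsory, it covers the study as well as the intervention, and nothing in the section confines it to the milder reading.

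**Conclusion.** The point holds in a limited form. The withdrawal section, followed as written, loses three-month SHARE-FI, CFS and muscle mass for randomised participants, for post-randomisation reasons that can depend on arm or on deterioration. It is at odds with the intention-to-treat analysis of all randomised and with the three-month visit for all.

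The clearest cases are care-home admission, which is both a ground for ineligibility and an outcome, and adverse events that stop the intervention, which belong to one arm. How many would be withdrawn as ineligible cannot be estimated from the protocol. For non-compliance the ceiling is about 23 to 36 of 105 intervention participants, against about 16 allowed for dropout. It rests on the broad reading of compliance, on the feasibility rates carrying over, and on every non-adherer being withdrawn.

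A reader might infer a definite bias in favour of the intervention. The protocol does not say that non-compliers do worse, so neither the size nor the direction of that part of the bias can be established from it.

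**What to change.** Reconcile the withdrawal section with Analysis sets by splitting the rule in two:

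- **Stopping the intervention.** Leave the clinical grounds as they are. State that stopping does not end follow-up.
- **Leaving the study.** Remove lack of compliance and ineligibility, whether arising or discovered later, as grounds. State that the three-month SHARE-FI, CFS and bioimpedance measurements, and hospitalisation and long-term care data, are collected on every randomised participant except those who withdraw consent for follow-up, die or cannot be traced.

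Non-compliance and ineligibility should still be recorded, so that the per-protocol set can be formed from them.

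The cost is amendment wording, with submission to the ethics committee, and a few more of the three-month visits already scheduled. The planned 176 and 210 do not change.

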### Study methods, assessments and procedures

GP site investigators will undergo three team-based training sessions prior to enrolment, monthly meetings after enrolment and additional ad-hoc meetings when required, led by the principal investigator, in order to standardise the approach and align to this study protocol, including patient communication, intervention delivery and data gathering and management.

Adults attending a GP surgery, meeting the eligibility criteria, will be offered general information about the study by the attending GP. If interested and willing to consent, they will be offered an information leaflet for the trial, and invited to participate. Participants will be randomly assigned to ‘intervention’ or ‘usual care’ parallel arms.

Participants randomly assigned to the usual care group will receive normal primary care, including physical rehabilitation if needed.

Intervention participants will be provided a leaflet with strength exercises and a discussion on how strength exercises have been shown to delay and reverse frailty and build resilience. The information leaflet will have a photographic overview of a home-based exercise regime. They will also be provided with information on post exercise protein consumption as part of a normal balanced diet.

Baseline measurements for all recruited patients will be: age, sex, education, living arrangement (alone, with others), smoking status, alcohol intake, blood pressure, heart rate, BMI (weight and height), comorbidities, malnutrition universal screening tool (MUST), CFS, SHARE-FI (which includes handgrip strength) and bioelectrical impedance for muscle mass, body fat, bone weight, base metabolic rate and ‘biological age’. Bioelectrical impedance will be measured using a Tanita RD 545 Segmental Body Composition Analyser, with dual frequency technology and medical grade accuracy.

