Intervention participants will be called after one month and after three months by the GP and asked if they had followed the exercise regime (and for how long and how many times a week) and dietary guidance. At three months they will be asked if they found the exercises ‘very easy’, ‘somewhat easy’, ‘neither easy nor hard’, ‘somewhat hard’, or ‘very hard’; and had they noticed any subjective difference to their health as a result of the intervention, namely feeling ‘much better’, ‘slightly better’, ‘about the same’, ‘slightly worse’ or ‘much worse’. All participants will be invited to return at three months for a clinical assessment and measurement of health indicators and frailty status as described above by the GP. Participants will be invited to return for subsequent one year follow up appointments. This 12-month follow up will be subject to a further ethics committee review. The follow up visits will be free of charge. A schedule of events for baseline, one-month call and three months follow up are shown in
Figure 3.

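### Withdrawal for loss to follow-up is mandatory but tied to no time point, and only the intervention arm has a scheduled contact before month 3, so primary outcomes could go uncollected earlier in that arm

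*Protocol article*

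**What the plan says.** The section *Discontinuation/withdrawal of subjects from study protocol* opens its list with a mandatory instruction: "Subjects must discontinue the intervention and be withdrawn from the study for any of the following reasons". One item on the list is "lost to follow-up. At least three documented attempts must be made to contact any subject lost to follow-up". The item covers both arms. It names no visit, time point or event from which loss is judged.

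*Study methods, assessments and procedures* sets the contacts:

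- Intervention arm: "Intervention participants will be called after one month and after three months by the GP".
- Usual-care arm: "Participants randomly assigned to the usual care group will receive normal primary care, including physical rehabilitation if needed". No study contact before month 3 is described.
- Both arms: "All participants will be invited to return at three months for a clinical assessment and measurement of health indicators and frailty status".

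*Analysis sets* then states: "Final analysis for this trial will be conducted on the intention-to-treat population, which will include all subjects randomised to the treatment arms". The section on missing data provides for chained-equations imputation where appropriate.

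**The concern.** The mandatory consequence, the undefined trigger and the unequal contact schedule combine badly. The only described point before month 3 at which anyone can be found unreachable exists in one arm. If a GP treats repeated unanswered calls at month 1 as loss to follow-up, the withdrawal section requires that person to leave the study two months before the primary assessment. A usual-care participant in the same position would simply be invited at month 3.

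The protocol describes assessment after withdrawal only for adverse-event cases, in the withdrawal section and in *Reporting procedures for all adverse events*. A person declared lost at month 1 therefore has no stated route to a month-3 SHARE-FI measurement, although such people are patients of the practice and may well attend.

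What is at stake is selective missingness of the primary outcome. People unreachable at month 1 may be less engaged or less well than those reached. If so, the intervention participants measured at month 3 would be a favourable subset. Imputation that assumes data are missing at random does not correct loss driven by disengagement that was never recorded.

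**Working it through.** **1. The sections side by side**

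| Point | Intervention | Usual care |
|---|---|---|
| Withdrawal if lost to follow-up | mandatory | mandatory |
| Time at which loss is judged | not stated | not stated |
| Scheduled study contact at month 1 | GP call | none described |
| Scheduled contact at month 3 | GP call and visit | visit |
| Earliest scheduled contact at which a person can be found unreachable | month 1 | month 3 |

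The rule is the same for both arms, but the schedule makes its earliest application differ. The figure with the schedule of events is not available here and might qualify the table; the text describes only these contacts.

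**2. The plan's own figures reproduce**

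Inputs from *Determination of sample size subjects*: 15% against 3%, 1:1 allocation, type I error 0.05, power 80%, total 176, enrolment 210, drop-out 15%. A two-sided test is assumed, as the text does not say.

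n per arm = [1.960·√(2·0.09·0.91) + 0.842·√(0.15·0.85 + 0.03·0.97)]² / 0.12² ≈ 88.1.

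That is 89 per arm (178 in total) when rounded up. With 88 per arm (176) power is 79.96%. For drop-out, 176/0.85 = 207.1, or 208 with equal arms, close to 210. Neither figure is in dispute.

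**3. Illustration of size**

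The documents give no rate of unreachable participants at month 1. The rates below are assumptions. So is the extreme condition that nobody lost in this way would have become non-frail and that there is no matching loss in usual care.

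*(a) No true effect.* Take 9% in both arms, the mid-point of 15% and 3%. The rate among intervention completers is 0.09/(1 − u), where u is the proportion lost early:

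- u = 5%: 0.09/0.95 = 9.5%
- u = 10%: 0.09/0.90 = 10.0%
- u = 15%: 0.09/0.85 = 10.6%

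The shift is about 0.5 to 1.6 percentage points, against a design difference of 12 points.

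*(b) Planned effect.* Take 105 per arm, the planned 15% loss in both arms (89.25 remaining per arm), and an extra early loss x in the intervention arm only. The observed intervention rate is 0.15·0.85/(0.85 − x). Power is Φ[(0.12 − 1.96·SE₀)/SE₁], where SE₀ uses the pooled rate and SE₁ the separate rates, with the true 15% and 3% kept, so that only the loss of numbers counts:

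| x | Intervention remaining | Observed rate | Power |
|---|---|---|---|
| 0 | 89.25 | 15.0% | 80.5% |
| 2% | 87.15 | 15.4% | 80.2% |
| 5% | 84.0 | 15.9% | 79.6% |
| 10% | 78.75 | 17.0% | 78.6% |
| 15% | 73.5 | 18.2% | 77.5% |

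The loss of power is minor. The issue is which outcomes are missing.

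**The case against.** A reader might infer that the protocol forces withdrawal after three failed calls and so removes unreachable people from the intervention arm only. The documents do not support that, for four reasons.

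- The three attempts are a minimum effort to be documented, which guards against declaring loss too soon. They are not a trigger.
- No section equates a missed one-month call with loss to follow-up. That call asks about exercise and diet and measures no frailty outcome. The commitment "All participants will be invited to return at three months for a clinical assessment" supports the ordinary reading that a person is lost when the outcome visit cannot be obtained.
- The rule covers both arms, and usual-care participants can be declared lost at month 3.
- Withdrawal does not take anyone out of the intention-to-treat set. The result is a missing value, to be imputed where appropriate. The rates worked out for completers therefore do not describe the stated main analysis.

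All four points stand. So does the remark that the magnitudes stack unfavourable assumptions. Nor does setting such losses against the 15% drop-out allowance show any excess, since unreachable people are among those the allowance is meant to cover.

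It can also be said that a journal article leaves the timing of such declarations to the full protocol, and that GP training and monthly meetings would settle it. This carries less weight. The article does not merely omit a definition: it states a mandatory rule which, beside its own contact schedule, can work unequally between arms. An analysis plan written later cannot recover outcomes that were never sought.

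Finally, the separate item on lack of compliance could still lead to withdrawal of a disengaged participant, so amending the loss-to-follow-up item alone would be incomplete. That is correct, and the fix allows for it.

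**Conclusion.** The point holds in a limited form. Mandatory withdrawal without a time point, combined with a one-month contact in one arm only, allows earlier and unequal loss of the primary outcome in the intervention arm. It sits badly with the invitation of all participants at three months and with the intention-to-treat analysis. The protocol permits this outcome but does not require it.

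The size is unknown and probably small. Under the assumed 5% to 15% early loss, with no improvers among those lost and none lost in the same way from usual care, the apparent rate among intervention completers moves by about 0.5 to 1.6 points from a common 9%. At the planned effect, power falls from 80.5% to between 79.6% and 77.5%. A bias towards the intervention is plausible if unreachable people are the less engaged or less well, but nothing in the documents establishes this. The point is worth correcting because the remedy costs almost nothing and the missing outcomes could not be recovered afterwards.

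**What to change.** Reconcile *Study methods, assessments and procedures* with *Discontinuation/withdrawal of subjects from study protocol* by stating that:

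1. a missed one-month call is recorded as a missed call and does not lead to withdrawal from outcome follow-up;
2. loss to follow-up is declared in both arms at the same point only, after a missed three-month visit and at least three documented failed attempts that follow it. The trigger should be the visit, because the three-month call is also made in the intervention arm only;
3. every randomised participant who has not withdrawn consent to follow-up is invited to the three-month assessment;
4. the other mandatory-withdrawal items, including the one on compliance, are reworded so that for outcome collection they agree with item 3. Clinical decisions on stopping the intervention remain with the investigators and are not affected.

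The cost is a few sentences in the protocol, a formal amendment through the ethics committee, and a mention in the GP training already planned. The three-month invitation is already foreseen for all participants. The only possible extra work is assessing some people who would otherwise have been withdrawn.
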